### 13.6 Tumor Marker Evaluation

In addition to the clinical endpoints, this study also will seek to answer translational questions with the idea of generation hypotheses for further testing. Each marker will be evaluated with respect to its prognostic value on PSA failure and overall patient survival. There will be 2 separate analyses, the first occurring when the PSA failure data from the clinical study is mature and the second when the survival data is mature.

#### 13.6.1 Correlation of Biomarkers with PSA Failure

We wish to determine the prognostic impact of each marker on time to PSA failure. This analysis will take place when each patient potentially has been followed for a minimum of 5 years, to correspond with the major clinical analysis of PSA failure. Multivariate Cox models will be used to evaluate the prognostic significance of each marker. The model will contain treatment and the stratifying variables (*combined Gleason score/PSA and Radiation Modality*) as fixed covariates. (9/18/03)

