### **1.2 Dose Response**

Retrospective data from single institution series and the Patterns of Care analysis have suggested that prostate cancer is a dose responsive neoplasm: the higher the dose of radiation administered to the tumor, the more likely it is to attain local tumor control. With the availability of 3D-CRT, it is felt that the higher radiation doses achievable using this modality will improve local tumor control in patients with localized adenocarcinoma of the prostate. Local control is a critical endpoint in the management of patients with prostate cancer. Fuks, et al. have demonstrated that local tumor progression serves as a nidus for the development of subsequent distant metastases and may ultimately compromise patient survival.

Higher doses of radiation have been known to increase cancer control in patients with adenocarcinoma of the prostate. Unfortunately, high doses without careful conformal treatment planning leads to higher complication rates. As described above, the RTOG and single institution studies have demonstrated that higher doses of radiation therapy can be safely administered using 3D-CRT. In the single institution prospective phase I/II dose escalation trials, investigators at FCCC and MSKCC have reported that the higher radiation doses are leading to an improved biochemical disease-free survival in patients with localized prostate cancer. Doses in excess of 75.6 Gy to the prostate improve freedom from biochemical recurrence and local disease progression. Radiation dose administered to the target volume was as important a prognostic factor in both of these series as was PSA, clinical stage, and Gleason score.

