### **1.6 Collection Of Tissue For Translational Research**

The RTOG has been collecting pretreatment diagnostic tissue from all of the prostate cancer protocols over the last ten years. A number of histologic, cell kinetic/proliferation, and molecular markers are under investigation, with several showing promise for the stratification of patients in future trials. This large randomized study presents an excellent opportunity for the collection of diagnostic biopsy specimens that will be assayed for various cytogenetic or gene expression abnormalities. Correlating these findings with clinical outcome in a group of men treated with radiation alone may help increase our understanding of radiation sensitivity or resistance. Along these lines, prospective and retrospective translational components will be applied to this randomized dose trial.

The prospective component will include measurements of serum testosterone, percent free PSA, prostate volume (obtained through planning CT-scans), percent of diagnostic biopsies involved, percent of cancer in the diagnostic biopsies, perineural invasion, mitotic index, and DNA-ploidy. The rationale for these markers is briefly provided.

A high pretreatment serum testosterone level has been associated with an increased risk of distant metastasis in prostate cancer patients treated with radiotherapy. The percent free PSA is an important aid in diagnosis and has potential as a prognostic factor; although it has not been investigated previously. Prostate volume will be used to examine PSA density and Vca, both of which have never been assessed prospectively in a large prostate cancer trial. The histopathologic parameters mentioned above have all shown promise in the past. The intent here is to request the collaborating pathologists at participating RTOG institutions and affiliates to record these parameters, with the goal of comparing these data with parallel central review. DNA-nondiploidy has repeatedly been shown to be a correlate of poor outcome; however, there are few studies involving radiotherapy therapy-treated patients. An application for funding will be made for the DNA-ploidy analysis.

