Retrospective analyses of several tissue biomarkers will also be performed. The biomarkers currently under study include Ki67, p53, bcl2, Bax, p21, pRb, p16, Cox-2, EBFR, and VEGF (*See reference 23 for review*). All of these markers show promise for providing prognostic information that compliments the standard clinical parameters of PSA, Gleason score and stage. Since diagnostic tissue will be limited, a final selection of the most promising markers will be made upon the completion of the ongoing studies involving the completed protocols 85-31, 86-10, 92-02, and 94-13. Approximately 7 years will be required for the proposed protocol to mature and by that time, a clearer definition of the markers to be studied will be evident. The goal will be to analyze approximately 8 biomarkers from the pretreatment diagnostic material.

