## **3.0 PATIENT SELECTION**

### **3.1 Conditions for Patient Eligibility**

- 3.1.1 Histologically confirmed prostate adenocarcinoma within 180 days of randomization;
- 3.1.2 Zubrod Performance Scale 0-1;
- 3.1.3 Prostatic biopsy tumor grading by the Gleason Score Classification;
- 3.1.4 One of the following combinations of factors:
- Clinical stage T1b-T2b, Gleason score 2-6, and prostate-specific antigen  $\geq 10$  but  $< 20$ ;
  - Clinical stage T1b-T2b, Gleason score 7 and prostate-specific antigen  $< 15$ ;
- 3.1.5 Pretreatment evaluations must be completed as specified in Section 4.1; (9/18/03)
- 3.1.6 Patients must sign a study-specific informed consent form prior to randomization.

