## 13.2 Sample Size

**13.2.1** *Stratification:* Patients will be stratified before randomization with respect to PSA and Gleason score: Gleason score 2-6 and PSA  $\geq 10$  but  $< 20$  vs. Gleason score 7 and PSA  $< 15$ , and Radiation Modality: 3D-CRT vs. IMRT. The treatment allocation scheme described by Zelen will be used because it balances patient factors other than institution. Patients will be randomized to MTD 3D-CRT or IMRT dose (79.2 Gy) vs. standard dose 3D-CRT or IMRT (70.2 Gy). (9/18/03)

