### 13.5 Inclusion of Minorities

In conformance with the national Institutes of Health (NIH) Revitalization Act of 1993 with regard to inclusion of women and minorities in clinical research, we address this issue here, as we will also analyze treatment differences in this male cohort by ethnicity. Based on previous RTOG prostate protocol data the minority enrollment for this study is expected as follows:

| Ethnic Group                              | Number      | Percent (%) |
|-------------------------------------------|-------------|-------------|
| American Indian or Alaskan Native         | 3           | 0.2         |
| Asian                                     | 8           | 0.5         |
| Black or African American                 | 228         | 15.0        |
| Hispanic or Latino                        | 46          | 3.0         |
| Native Hawaiian or other Pacific Islander | 4           | 0.3         |
| White                                     | 1216        | 80.0        |
| Other/Unknown                             | 15          | 1.0         |
| Total                              | 1520 | 100  |

Obviously with 80% of the available sample being white, univariate comparisons by treatment will not yield sufficient power in most cases. We will, however, also include the ethnicity variable in all regressions including the Cox model.

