#### 13.6.2 Correlation of Biomarkers with Overall Survival

We wish to determine the prognostic impact of each marker on time to overall survival. This analysis will take place when each patient has been potentially followed for a minimum of 8 years, to correspond with the major clinical analysis of the primary endpoint, overall survival. Multivariate Cox models will be used to evaluate the prognostic significance of each marker. The model will contain treatment and the stratifying variables (*combined Gleason score/PSA and Radiation Modality*) as fixed covariates. (9/18/03)

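### The marker Cox models in 13.6.1 and 13.6.2 omit measured PSA, T stage and, for survival, age, so as written they cannot show that a marker adds to PSA, Gleason score and stage

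*Protocol*

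**What the plan says.** Section 13.6 says each marker will be assessed for prognostic value on PSA failure and overall survival, and describes the work as hypothesis-generating. Section 13.6.1 then fixes the Cox model for PSA failure: "The model will contain treatment and the stratifying variables", which it lists as combined Gleason score/PSA and radiation modality. Section 13.6.2 opens with "We wish to determine the prognostic impact of each marker on time to overall survival" and uses the same covariates. Section 13.5 adds one more term, since the protocol will "also include the ethnicity variable in all regressions including the Cox model".

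The stratum is defined in section 13.2.1: "Patients will be stratified before randomization with respect to PSA and Gleason score". It has two levels: Gleason 2-6 with PSA from 10 to below 20, and Gleason 7 with PSA below 15. Section 3.1.4 allows the same stage range in both levels; the second reads "Clinical stage T1b-T2b, Gleason score 7 and prostate-specific antigen" below 15.

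Section 1.6 explains why the tissue markers are of interest: they show promise for "prognostic information that compliments the standard clinical parameters of PSA, Gleason score and stage". It also says that correlating markers with outcome in men treated with radiation alone "may help increase our understanding of radiation sensitivity or resistance". Section 1.2 reports that dose was as important a prognostic factor in two series "as was PSA, clinical stage, and Gleason score". Section 13.2.2 bases its survival assumptions on published risk groups built from independent predictors of death, T stage among them.

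**The concern.** The rationale and the fixed model do not match. To show that a marker adds to PSA, Gleason score and stage, those three factors must be in the model beside it. Here the only disease factor is the two-level stratum. Stage is absent, PSA enters only through broad overlapping bands, and Gleason 2 to 6 is one category. For death from any cause, age is absent too.

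Some of the listed markers are tied to PSA by construction. Section 1.6 includes percent free PSA, and prostate volume so that PSA density can be examined. For these, correlation with PSA inside a stratum is to be expected.

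The two biomarker correlations are listed secondary endpoints in section 13.1.2, and section 1.6 speaks of using such markers to stratify patients in future trials. A marker that restates PSA or stage would be of little use for that, yet this model could present it as prognostic.

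**Working it through.** **1. Reading the model.** Sections 13.6.1 and 13.6.2 give no sample size, power or effect size, so there is no figure of the plan's own to reproduce. The factors compare as follows.

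| Factor | In the model as written? |
|---|---|
| Dose arm, modality | Yes (13.6.1, 13.6.2) |
| Ethnicity | Yes (13.5) |
| Gleason 2-6 versus 7 | Yes, through the stratum |
| PSA within a stratum | No |
| T stage | No |
| Age (all-cause death) | No |
| Marker by dose arm | No |

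**2. Event counts.** Table 3 projects 316 to 338 PSA failures at year 7. As a check I used its inputs: N = 1410, five-year accrual, λ = 0.074 per year in the control arm, and μ = 0.02 per year for deaths without PSA failure. Expected failures per arm are (N/2) × the average over follow-up t of λ/(λ+μ) × (1 − exp(−(λ+μ)t)), with λ divided by the hazard ratio in the high-dose arm. This gives 338, 329, 325, 321 and 315, against the stated 338, 331, 326, 321 and 316. The marker analysis in 13.6.1 comes later, at a minimum of five years of follow-up (about year 10), where the same formula gives 473 to 505.

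**3. Size of the spurious association.** Take a marker with no effect of its own and correlation ρ with log PSA within stratum. Approximately, its log hazard ratio per SD is ρ × ln(HR of PSA per SD), and z = that × √(events). The chance of p<0.05 is Φ(z − 1.96) + Φ(−z − 1.96).

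Assumptions not in the documents: ρ = 0.3; PSA uniform on 10-20 and on 3-15 in the two levels; PSA hazard ratio 1.65 to 2.2 per log unit. The SD of log PSA is then 0.198 and 0.437. Weighting the variances 44/56 (the split in 13.2.2) gives √(0.44 × 0.198² + 0.56 × 0.437²) = 0.352. The hazard ratio per SD is 1.65^0.352 = 1.19 to 2.2^0.352 = 1.32. A value of 1.5 is carried as an upper bound.

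| PSA HR per SD | Marker log HR | z, 330 failures | Chance of p<0.05 |
|---|---|---|---|
| 1.19 | 0.3 × 0.174 = 0.052 | 0.95 | 16% |
| 1.32 | 0.3 × 0.278 = 0.083 | 1.51 | 33% |
| 1.5 | 0.3 × 0.405 = 0.122 | 2.21 | 60% |

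At 492 failures (year 10, treatment hazard ratio 1.4), z becomes 0.052 × 22.2 = 1.16 at the low end and 0.122 × 22.2 = 2.70 at the high end, so the range is 21% to 77%. If only half the patients have tissue (165 failures at year 7), it is 10% to 35%.

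**4. Simulation of the remedy.** Cox models were fitted to simulated trials of 1410 patients with about 500 PSA failures. The marker had no effect of its own and was correlated with both log PSA and stage. Further assumptions were stage hazard ratios of 1.35 to 1.65, 45% with higher stage and 40% IMRT. There were 150 replicates per setting.

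| Correlation with each | Model as written | With log PSA and stage added |
|---|---|---|
| 0.2 | 21% to 56% | 8% to 9% |
| 0.4 | 73% to 99% | 9% |

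The Monte Carlo standard error of the right-hand column is about 2 points. With zero correlation (300 replicates) both models rejected in 6% to 7%.

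**The case against.** The strongest reply is that these are exploratory analyses with a prognostic aim. Section 13.6 calls them hypothesis-generating, and no primary analysis, sample size or stopping rule depends on them. Eligibility already narrows PSA, Gleason score and stage. Saying what the model will contain does not forbid more terms, and an analysis plan not shown here could add them. All of this limits the weight of the point. It does not remove it: the protocol does name a covariate set, and that set does not fit the purpose it gives.

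Three stronger readings are tempting, and the documents do not support them.

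- **That the stratum adjusts for neither Gleason score nor PSA.** It conditions exactly on Gleason 2-6 versus 7. A coefficient that mixes the two effects does not undo that. What is left is PSA within level, finer Gleason detail, stage and age.
- **That omitting a marker-by-dose term contradicts the plan.** Objective 2.2.5 and section 13.6 ask about influence on outcome after radiation and about prognostic value. Section 1.6 says only that the correlations may help in understanding radiosensitivity. A pooled main effect cannot separate radiosensitivity from general prognosis, but the protocol does not claim that it does. Such a term would also have little power. With a 50/50 marker, 80% power and two-sided 0.05, the detectable ratio of hazard ratios is exp(2.80 × √(16/492)) = 1.66 if all patients have tissue, and 2.04 if half do.
- **That a 60% false-positive rate is the expected result.** It is the top of an assumed range. A hazard ratio of 1.5 per SD in the PSA 10-20 level (SD 0.198) means risk rising 1.5^(0.693/0.198), about 4.1-fold, per doubling of PSA. Under the PSA spread assumed above, 16% to 33% is the more moderate range.

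**Conclusion.** The point holds in a limited form. With the two-level stratum as the only disease factor, the models as written cannot show that a marker adds to PSA, Gleason score and stage, and a marker that tracks PSA or stage within a stratum can appear prognostic. At a correlation of 0.3 and 330 PSA failures, the chance of a nominally significant result for a marker with nothing to add is roughly 16% to 60%, against 5%. More events at the planned minimum five-year follow-up raise it, and incomplete tissue collection lowers it.

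These are false positives for added value. The association within stratum would be genuine, but it would belong to PSA or stage. The correlations, hazard ratios and PSA distribution are assumptions, so the figures show direction and range only. The omission itself is read directly from the text. This is a worthwhile correction to two secondary, hypothesis-generating analyses and does not affect the trial's main conclusions.

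**What to change.** In 13.6.1 and 13.6.2, fit each marker in a Cox model with treatment, radiation modality, ethnicity, log PSA as a continuous term, Gleason score, T stage and age, in place of reliance on the two-level stratum. Report whether adding the marker improves on the clinical model without it, for example by a likelihood-ratio test. Optionally, state that a marker-by-dose-arm term will be examined as exploratory, with its low power acknowledged.

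The cost is a wording change and a few degrees of freedom against several hundred events. No new data are needed: PSA, Gleason score and T stage are on the eligibility checklist, and date of birth and race are recorded at registration.

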#### 13.6.2 Correlation of Biomarkers with Overall Survival

We wish to determine the prognostic impact of each marker on time to overall survival. This analysis will take place when each patient has been potentially followed for a minimum of 8 years, to correspond with the major clinical analysis of the primary endpoint, overall survival. Multivariate Cox models will be used to evaluate the prognostic significance of each marker. The model will contain treatment and the stratifying variables (*combined Gleason score/PSA and Radiation Modality*) as fixed covariates. (9/18/03)

## **APPENDIX II**

### **KARNOFSKY PERFORMANCE SCALE**

|     |                                                                              |
|-----|------------------------------------------------------------------------------|
| 100 | Normal; no complaints; no evidence of disease                                |
| 90  | Able to carry on normal activity; minor signs or symptoms of disease         |
| 80  | Normal activity with effort; some sign or symptoms of disease                |
| 70  | Cares for self; unable to carry on normal activity or do active work         |
| 60  | Requires occasional assistance, but is able to care for most personal needs  |
| 50  | Requires considerable assistance and frequent medical care                   |
| 40  | Disabled; requires special care and assistance                               |
| 30  | Severely disabled; hospitalization is indicated, although death not imminent |
| 20  | Very sick; hospitalization necessary; active support treatment is necessary  |
| 10  | Moribund; fatal processes progressing rapidly                                |
| 0   | Dead                                                                         |

### **ZUBROD PERFORMANCE SCALE**

- 0 Fully active, able to carry on all predisease activities without restriction (*Karnofsky 90-100*).
- 1 Restricted in physically strenuous activity but ambulatory and able to carry out work of a light or sedentary nature. For example, light housework, office work (*Karnofsky 70-80*).
- 2 Ambulatory and capable of all self-care but unable to carry out any work activities. Up and about more than 50% of waking hours (*Karnofsky 50-60*).
- 3 Capable of only limited self-care, confined to bed or chair 50% or more of waking hours (*Karnofsky 30-40*).
- 4 Completely disabled. Cannot carry on any self-care. Totally confined to bed or chair (*Karnofsky 10-20*).

### APPENDIX III

#### AJCC STAGING SYSTEM PROSTATE, 5th Edition

##### DEFINITION OF TNM

###### Primary Tumor, Clinical (T)

|     |                                                                                                                                                             |
|-----|-------------------------------------------------------------------------------------------------------------------------------------------------------------|
| TX  | Primary tumor cannot be assessed                                                                                                                            |
| T0  | No evidence of primary tumor                                                                                                                                |
| T1  | Clinically inapparent tumor not palpable or visible by imaging                                                                                              |
| T1a | Tumor incidental histologic finding in 5% or less of tissue resected                                                                                        |
| T1b | Tumor incidental histologic finding in more than 5% of tissue resected                                                                                      |
| T1c | Tumor identified by needle biopsy ( e.g., because of elevated PSA )                                                                                  |
| T2  | Tumor confined with prostate*                                                                                                                               |
| T2a | Tumor involves one lobe                                                                                                                                     |
| T2b | Tumor involves both lobes                                                                                                                                   |
| T3  | Tumor extends through prostate capsule**                                                                                                                    |
| T3a | Extracapsular extension ( unilateral or bilateral )                                                                                                  |
| T3b | Tumor involves the seminal vesicle(s)                                                                                                                       |
| T4  | Tumor is fixed or invades adjacent structures other than the seminal vesicles: bladder neck, external sphincter, rectum, levator muscles and/or pelvic wall |

\*Note: Tumor found in one or both lobes by needle biopsy, but not palpable or reliably visible by imaging, is classified as T1c

\*\*Note: Invasion into the prostatic apex or into (*but not beyond*) the prostatic capsule is not classified as T3, but as T2.

###### Regional Lymph Nodes (N)

|    |                                            |
|----|--------------------------------------------|
| NX | Regional lymph nodes cannot be assessed    |
| N0 | No regional lymph node metastasis          |
| N1 | Metastasis in regional lymph node or nodes |

